## Abstract

**Background and Objectives:**

Cognitive and emotional changes affect the majority of individuals with acquired brain injury (ABI) and are associated with poorer outcomes. The evidence for “siloed” rehabilitation approaches targeting cognition and mood separately remains mixed. Valued living (i.e., acting consistently with personal values) is associated with better psychological functioning and participation in work and other productive activities. Rehabilitation interventions that concurrently address cognitive and emotional barriers to valued living may therefore result in improved outcomes. VaLiANT (Valued Living After Neurological Trauma) is an 8-week group intervention developed by our team, which uniquely combines cognitive rehabilitation and psychological therapy to improve wellbeing and meaningful participation (i.e., valued living) following ABI.

**Method:**

This protocol describes the design and implementation of a Phase II parallel-group randomized controlled trial with blinded outcome assessors, to evaluate the potential efficacy of VaLiANT and the feasibility of a Phase III trial. Participants are adults with a history of ABI at least 3 months prior to study entry, who experience cognitive and/or emotional difficulties and associated reduced participation in valued activities. Random allocation to the treatment condition (8-week VaLiANT group program) or a usual care waitlist control condition occurs at a 2:1 treatment: control ratio. The primary outcome is wellbeing, measured by the Warwick-Edinburgh Mental Wellbeing Scale. Secondary outcomes include measures of valued living, mood, cognitive complaints, quality of life, community participation, post-traumatic growth, and self-efficacy. All measures are collected across three time points by blinded assessors (baseline, 8-week follow-up, 16-week follow-up). Trial feasibility will be evaluated against recruitment rates, drop-out rates, intervention acceptability, and treatment fidelity (manual adherence and therapist competence).

**Discussion:**

This trial will extend current knowledge on how to improve long-term outcomes following ABI by evaluating an innovative integrated, multi-domain approach to rehabilitation concurrently addressing cognitive and emotional barriers to participation in meaningful life roles.

## Introduction

Acquired brain injuries (ABIs) such as stroke and traumatic brain injury (TBI) frequently result in cognitive and emotional changes. Estimates suggest that over half of those with a TBI or stroke experience long-term cognitive impairment, especially in the domains of attention, memory, and executive functions (1, 2). Similarly, clinically significant levels of depression and anxiety affect one-third of stroke and half of TBI survivors (3–5) and rates of suicide following ABI are notably higher (6). These cognitive and emotional difficulties are interrelated and highly comorbid after ABI (7), with higher mood symptoms predicting increased cognitive complaints (8), and increased cognitive complaints predicting higher mood disturbance (9). Cognitive and emotional sequelae are frequently highlighted as areas of long-term unmet need by people with ABI, indicating that they are not managed adequately by existing services (10, 11).

Importantly, cognitive impairment and mood disturbance are associated with poor long-term outcomes following ABI. Cognitive impairment predicts reduced independence in activities of daily living (ADLs), reduced participation in meaningful life activities, and poorer overall quality of life (12–15). Furthermore, cognitive impairment is a stronger predictor of negative outcomes and overall disability at 5–10 years post-ABI than the initial injury severity (16, 17). Mood symptoms also predict reduced independence in ADLs, participation in meaningful life activities (18–21), and poorer quality of life (22, 23). As such, cognitive impairment and mood disturbance act as significant barriers to adjustment and recovery from ABI, highlighting the need for evidence-based interventions that address these difficulties.

Current treatment approaches typically remain domain-specific and target cognitive impairment or mood symptoms in isolation, with a limited focus beyond the impairment level (24). Evidence for these approaches remains inconclusive, with studies demonstrating variable efficacy and limited generalization to broader outcomes. For example, memory interventions tend to result in moderate improvements to both subjective and objective memory performance following ABI (25) but provide mixed findings regarding improvement in long-term functional outcomes and quality of life (26–28). Interventions targeting attention deficits have resulted in limited improvement to attention immediately following interventions with no generalization to other long-term outcomes (29). Cognitive Behavioral Therapy (CBT) can improve depressive and anxiety symptoms and some functional outcomes following stroke (30) but these effects have not been consistently found after TBI (31), although adapted CBT that incorporated cognitive compensatory strategies including follow-up booster sessions has shown promise for treating anxiety and depression following TBI (32) with associated improvements in psychosocial outcomes (daily functioning, work, relationships, leisure). Therefore, existing “siloed” treatment approaches do not consistently demonstrate improvements to mood or cognition and positive intervention effects do not consistently translate into improved long-term outcomes such as quality of life or participation in meaningful activities.

It then follows that cognitive rehabilitation and psychological therapy techniques may need to be integrated to holistically improve outcomes beyond the impairment level by concurrently targeting cognitive and emotional barriers to activity and participation in meaningful life roles, wellbeing, and quality of life (33, 34). There is a growing body of evidence suggesting that integrated rehabilitation interventions that combine both psychological and cognitive elements into broader frameworks lead to improvements in psychological distress, meaningful participation, and quality of life, with stable or ongoing improvement up to 3 years following treatment (35, 36). Randomized controlled trial (RCT) level evidence has also suggested that such approaches are more effective at improving outcomes than standard neurorehabilitation and traditional neuropsychological intervention (37, 38). Patients have described experiencing holistic neurorehabilitation as empowering and beneficial for everyday functioning (39). However, several challenges continue to limit the implementation of such interventions including a lack of funding, resources, or other systemic factors (34). The aforementioned interventions were all lengthy with a high frequency of sessions [e.g., 15 h per week over 16 weeks; (37)] which may not be easily implemented or appropriate for all health-care systems. Further research is needed to determine whether the positive effects of integrated, holistic interventions can be replicated when the length of intervention is briefer, which may be more cost-effective and more readily implemented into existing services.

Valued living refers to the extent to which we engage in behaviors that are consistent with our personal values, and it has gained growing attention as an important outcome post-ABI. Higher levels of valued living have been linked with improved wellbeing, quality of life, better psychosocial functioning, and lower psychological distress in both ABI (40, 41) and other chronic health condition populations (42–44). Valued living has been directly related to the level of acceptance and adjustment toward one's ABI (45). However, valued living often remains reduced for a number of years following brain injury (40). Rehabilitation interventions that target valued living may result in improved outcomes. Acceptance and Commitment Therapy (ACT) is an evidence-based psychological therapy that directly targets valued living, with growing evidence supporting its use to improve mood symptoms and psychological distress in TBI (46–49), stroke (50–52) and other neurological conditions (53, 54). However, none of these studies have specifically aimed to address cognitive impairment, and all have demonstrated limited impact beyond the level of mood disturbance and psychological distress.

A holistic and integrated intervention that targets both cognitive and emotional barriers to valued living may result in more consistent improvements to impairments (e.g., cognitive complaints or mood symptoms) while also leading to more global improvements in meaningful participation, wellbeing, and quality of life. Valued Living After Neurological Trauma (VaLiANT) is a new 8-week group intervention that aims to enhance adjustment to life with ABI by combining cognitive rehabilitation and psychological therapy using ACT principles. A Phase I study has been completed using a single case experimental design repeated across eight participants (55). This study demonstrated reliable improvements to a broad range of outcomes for the majority of participants, including overall wellbeing, anxiety symptoms, and subjective cognitive complaints. The delivery of the intervention was deemed feasible and participant acceptability ratings of the intervention were high. These Phase I findings suggested that VaLiANT may have utility in improving outcomes following ABI and warrants further investigation of the intervention.

Here, we report the protocol for our Phase II RCT evaluating VaLiANT, which aims to:

Compare the impact of VaLiANT against treatment-as-usual waitlist control on a range of adjustment-related outcomes including at the levels of impairment, activity, participation, and overall wellbeing and quality of life. This will identify signals of efficacy and determine parameter estimates for a definitive Phase III trial.Investigate the feasibility of the trial design, including recruitment rate, retention rate, success of blinding the outcome assessor under RCT conditions, and exploring the fidelity of delivering the intervention.

## Method

### Ethics

This study has been approved by the La Trobe University Human Research Ethics Committee (HEC #18423) and has been registered in the Australian New Zealand Clinical Trials Registry (ACTRN12619001243101). Protocol amendments have been submitted to both bodies following methodological changes due to the impact of COVID-19. Written informed consent will be obtained from all participants.

### Study Design

This Phase II pilot study is a prospectively registered single center, two-arm, assessor-blinded, parallel groups RCT, comparing outcomes of the 8-week VaLiANT group intervention with treatment-as-usual waitlist control. Outcome measures are collected at baseline (T1), at an 8-week follow-up (T2), and at a 16-week follow-up from baseline (T3). An overview of the study procedure is summarized in Figure 1. This protocol was developed in accordance with the Standard Protocol Items: Recommendations for Interventional Trials (SPIRIT) guidelines (56). Methodological modifications made due to the impact of COVID-19 have been reported in line with SPIRIT Extension for RCTs Revised in Extenuating Circumstances (CONSERVE-SPIRIT) guidelines (57) throughout the text and summarized in a separate paragraph. The methodological quality of the trial will be evaluated using the Physiotherapy Evidence Database – Psycbite (PEDro-P) scale upon completion of the trial (58).

**Figure 1 F1:**
[figure not shown]
Study flow diagram. VaLiANT, Valued Living After Neurological Trauma.

### Participants and Recruitment Process

This study is conducted at La Trobe Psychology Clinic (Melbourne, Australia); a psychology clinic at La Trobe University that also serves as a training clinic for postgraduate psychology students. Community-dwelling participants are identified either through self-referral or referral from a health professional. Recruitment methods include distribution of specific advertisement material (including flyers and weblinks) through local email listservs for clinicians/researchers who work with ABI (e.g., NPinOz, BRAINSPaN), local health services, practitioner networks, the Australian Stroke Clinical Registry (AuSCR), and relevant online portals for individuals living with ABI such as EnableMe (Stroke Foundation). Participants are required to be at least 3-months post-ABI (including stroke, TBI, brain tumor, hypoxic brain injury, and multiple sclerosis) before enrolment in the study; be 18 years of age or over; have reported cognitive and/or emotional difficulties (identified by self, close other and/or clinician in initial screening); and be able to attend the group program in person at La Trobe University Psychology Clinic or *via* telehealth during periods of COVID-19 related restriction. Exclusion criteria include pre-existing intellectual disability, severe psychiatric disorder, comorbid neurodegenerative condition, and insufficient cognitive and/or language abilities to complete outcome measures or participate in the intervention. Participant eligibility is determined *via* telephone screening conducted by the project coordinator (a trainee clinical neuropsychologist) prior to enrolment into the study.

### Intervention

The VaLiANT program is a manualized group intervention that concurrently targets cognition and emotion by integrating cognitive rehabilitation and ACT techniques to improve engagement in valued activities following ABI. The program consists of eight 2-h group sessions delivered either in-person or *via* telehealth during periods of COVID-19 restrictions, with group sizes ranging from three to eight participants. The intervention was developed by the authors, drawing on their clinical and research expertise, however evidence-based ACT and cognitive rehabilitation techniques and materials were adapted from existing manualized treatments to supplement the new content (46, 59–62). Group delivery was chosen due to a number of factors: 1) the cost-effectiveness compared to individual treatment, 2) the additional benefit of group discussion and the sharing of ideas for particular topics e.g., strategies to manage particular difficulties following ABI, and 3) to address social isolation and provide access to other individuals with shared experience. A number of small revisions were made to the manual and treatment delivery following completion of the Phase I study (55): 1) additional scaffolding was added in Session 2 to assist participants with linking their values to behavior, 2) a mindfulness exercise was included in every session (previously was in most but not all sessions), and 3) email reminders for the homework activities were sent to participants at the end of each calendar week. The treatment manual and resources will be published following completion of the trial. For more information on the intervention content and additional modifications made due to COVID-19, please see Tables 1, 2.

**Table 1 T1:** TIDieR checklist describing the Valued Living After Neurological Trauma intervention and telehealth modifications.

**Item**	**Telehealth modification**
*1. Name* Valued Living After Neurological Trauma (VaLiANT)	
*2. Why* Existing interventions that target cognition and mood separately have displayed variable effectiveness and limited generalizability to broader outcomes (e.g., participation and quality of life) which may relate to the lack of integration between cognition and emotional symptoms. Valued living has been associated with better functional and psychosocial outcomes and has been identified as a potential treatment target following brain injury. VaLiANT utilizes a combined therapeutic approach that targets both cognitive impairment and mood disturbance with an overall focus on improving valued living. This represents a novel approach to improving outcomes post brain-injury.	
*3. What (materials)* *Treatment manual:* Each therapist delivering the intervention has access to a treatment manual outlining the treatment objectives, content to be covered each week, participant handouts and materials, and homework activities. The manual provides detailed instructions on how to cover each treatment component or activity, including suggested wording or phrasing, and prompts for enhancing or directing discussions.	
*Participant worksheets and handouts:* Each week participants receive a hard-copy package of psychoeducational handouts, recordings of mindfulness activities, and worksheets that are completed during the session or between sessions.	During periods of telehealth delivery, these materials are provided electronically using either cloud-sharing or *via* email.
*PowerPoint slides:* Each session is supported by PowerPoint slides displayed on an electronic overhead projector. Participants receive printed copies of the PowerPoint slides with space to take written notes during sessions.	During periods of telehealth delivery these are provided electronically using either cloud-sharing or *via* email.
*Values cards:* Hard-copy values cards specifically designed for the intervention are provided to participants within session for values card-sorting activities.	During periods of telehealth delivery, the values cards and associated activities are accessed *via* a custom-made electronic application hosted on a cloud platform (http://www.heroku.com).
*Sultanas:* Sultanas are provided to participants within session for a mindful eating exercise in Session 3.	Participants are instructed to bring a dried fruit or similar substitute to the relevant session. This is included as part of their homework from the previous week and an email reminder is sent prior to the session.
*Materials for passengers on the bus exercise:* Post it notes and values cards are used for an *in-vivo* passengers on the bus exercise.	The materials are substituted for extra PowerPoint slides.
*Whiteboard:* A whiteboard is used within multiple sessions for group discussion and brainstorming activities.	The electronic whiteboard function on Zoom is used instead.
*Pens:* Participants are provided with pens to take written notes during sessions	Pens are not provided during telehealth delivery.
*Computer/tablet and internet:* Not applicable	Participants are required to have their own computer or tablet device with a webcam and stable internet connection.
*4. What (procedures)* Every week of the VaLiANT program focusses on a different value domain (e.g., health, work/productive activities, leisure, relationships). Each session begins with a review of the previous week's homework. Following this, participants explore and identify their important values in that week's value domain (*via* the card-sort activity) and select one value to focus on over the following week. Participants then generate SMART (specific, measurable, achievable, relevant to the value, and time-bound) goals or “committed actions” that are consistent with the chosen value and can be done over the coming week. This process is supported by the group facilitators. The remainder of each session focusses on facilitating implementation of committed actions. Psychoeducation and various activities are used to teach cognitive compensatory strategies and ACT techniques such as mindfulness, including in-session practice of those strategies. With further support from facilitators, participants identify potential cognitive or emotional barriers to their committed actions (e.g., forgetfulness or low motivation) and select appropriate strategies to enable valued living. Most activities involve group discussion to encourage reflection and exchange of ideas amongst participants. Weekly homework activities include completing the selected committed actions and other tasks that aim to increase implementation of taught strategies into everyday life. Further information on the content of each session can be found in Table 2 and the published outline of the treatment manual [(55); supplemental material].	
*5. Who Provided* The VaLiANT intervention is facilitated by a senior Clinical Neuropsychologist experienced in working with individuals with ABI and expertise in delivering group-based interventions, cognitive rehabilitation, and ACT. An additional two clinicians assist with facilitation of each group. These are primarily trainee psychologists assisting with the delivery of 1 – 2 groups as part of their postgraduate clinical neuropsychology or clinical psychology training. The assisting clinicians are provided with prior training and supervision by the senior facilitator including didactic instruction and observational learning by watching recordings of previous sessions. Quality of intervention delivery and group facilitation skills are monitored during each session by the senior facilitator, and feedback provided during supervision which occurs after every session.	
*6. How* The VaLiANT intervention is intended to be delivered in-person on a weekly basis in a group environment (ranging from 3 to 8 group members).	Following the onset of the COVID-19 pandemic, the intervention was redeveloped to be deliverable *via* telehealth using videoconferencing (Zoom).
*7. Where* In-person delivery of the intervention occurs at the La Trobe University Psychology Clinic (Melbourne, Australia).	Telehealth delivery of the intervention occurs in participants' homes, with facilitators either at the university or in their homes.
*8. When and How much* The intervention involves eight sessions that run weekly, for 2 h, over a period of 8–9 weeks (depending on breaks for public holidays).	
*9. Tailoring* The treatment manual is intended to be a flexible guide, whereby content can be tailored as long as key session objectives are met and key session components are delivered. For example, specific strategies for addressing cognitive and emotional barriers can be more strongly emphasized if several participants identify similar barriers (e.g., motivation) or only briefly covered if less relevant (e.g., word-finding strategies). There are other specific opportunities for tailoring of the intervention in particular sessions (e.g., additional “optional” activities to further explore core concepts) if the core content has been covered adequately with time remaining. This additional content is not required to cover the main concepts but allows some tailoring of the intervention depending on the abilities and preferences of group participants.	
*10. Modifications*	Telehealth adaptations included the development of an online program to present the values card sort task and associated weekly worksheet while also allowing facilitators to see what participants were doing in real time during these activities. This was essential to allow facilitators to support participants in generating committed actions in line with their chosen values. Due to the likelihood of technical difficulties and participants requiring additional assistance with the online tasks, the time allocated to some activities (e.g., identification of barriers) was reduced to allow more time for core components (e.g., strategies) to ensure that the key concepts were covered. Some strategies that are potentially not relevant for every participant (e.g., activity scheduling) were moved to “optional” discussions that are only covered if participants identify particular problems. Some activities were also modified slightly to allow for completion online e.g., a group experiential ACT exercise (“Passengers on the Bus”) which involves participants moving around the room became more discussion based.
*11. How well (planned)* All VaLiANT sessions are video recorded. To measure treatment fidelity, a random selection of at least 10% of the video-recorded intervention sessions will be assessed by an independent researcher trained in cognitive rehabilitation, Acceptance and Commitment Therapy and group interventions. They will evaluate whether clinicians were able to meet the session objectives and cover the prescribed content using a checklist based on the manual for each session (i.e., treatment adherence), as well as the clinicians' competence in group facilitation (i.e., therapist competence).	
Competency in group facilitation skills is assessed using the eNACT group facilitation competency checklist, a 4-point likert scale which measures the quality of the therapist's group facilitation across 16 skills from 0 = “skill not observed despite opportunity,” to 3 = “observed – done well” (63). An additional item was added to the checklist to assess whether facilitators had delivered the intervention in an ACT-consistent manner (“Therapist demonstrates psychological flexibility in interactions with participants i.e., shows openness, flexible self-awareness and engages in their own valued actions, even when difficult topics arise in the group”).	

*Item 12 [how well (actual): if intervention adherence or fidelity was assessed, describe the extent to which the intervention was delivered as planned] cannot be fully described until study completion and has been omitted*.

**Table 2 T2:** Overview of Valued Living after Neurological Trauma (VaLiANT).

**Session**	**Content**
1	**Introduction to the program** Overview of the program, intervention aims, and main components Establishment of group rules and group facilitator role Getting to know each other and sharing of stories Introduction to values, valued living Values card sort exercise Passengers on the bus exercise Mindfulness breathing exercise Introduction to committed actions and experiential avoidance Homework– self-monitoring form and name association task
2	**Being Healthy—Sleep and fatigue management** Introduction to “being healthy” module Values card sort exercise Discussion on four pillars of health Sleep and fatigue psychoeducation and strategies Mindfulness body scan exercise Experiential avoidance discussion (optional) Identification of committed actions and barriers Introduction to S.M.A.R.T goals Introduction to and completion of the “way to valued living worksheet” Homework—rest break scheduling and completing committed actions
3	**Being Healthy – Diet and exercise management** Review of values selected in previous session Way to valued living worksheet Diet and exercise psychoeducation Exploration of barriers Passengers on the bus exercise Mindful eating exercise Identification of committed actions Strategies for planning, memory, pacing, and motivation Activity scheduling exercise Homework—mindful eating and completing committed actions
4	**Having a Purpose—Work, study, or participation in the community** Overview to “having a purpose” module Values card sort exercise Identification of committed actions Identification of barriers Mindfulness self-compassion exercise Strategies for prospective memory and completing complex tasks Homework—prospective memory task and completing committed actions
5	**Having a Purpose—Leisure activities** Introduction to leisure exercise Psychoeducation on mood and the importance of leisure Values card sort task Exploration of leisure activities Identification of committed actions Mindfulness of the senses exercise Barriers to leisure exploration & associated strategies Homework—leisure activity schedule and completing committed actions
6	**Connecting with Others—Relationships part I** Overview of “relationships module” Values card sort task Identification of strengths in relationships Identification of committed actions Barriers exploration Mindfulness S.T.O.P exercise Strategies for cognitive communication difficulties Homework—planning a difficult conversation and completing committed actions
7	**Connecting with Others—Relationships part II (friends/family session)** *Friends/family members (1st h)* Introduction to VaLiANT Introduction to values and valued living Values card sort exercise Introduction to barriers and communication changes following brain injury Managing difficult emotions exercise *Participants (1st h)* Reflection on relationships and values they would like to bring Identification of committed actions Addressing social barriers Passengers on the bus exercise *All together (2nd h)* Mindfulness S.T.O.P exercise Strategies to support communication of abilities and needs Open communication discussion Homework – have an open conversation and completing committed actions
8	**Review and future directions—Tying it all together** Review of values, committed actions, strengths, and barriers identified in previous sessions Re-identification of helpful strategies from previous sessions Mindfulness S.T.O.P exercise Post-traumatic growth discussion (optional) Future support options Conclusion

*Each session begins with a review of the previous session's content and homework tasks (excluding Session 1). In session 7 participants have the ability to bring a family member or friend who complete separate activities for the 1st h, before joining participants to practice communication strategies in the 2nd h*.

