### Sample Size Calculation

A power analysis was conducted using 5,000 simulations within the SimR package for R (86) to determine if the maximum possible sample size during the data collection period (*N* = 64) was sufficient for the statistical analyses. A previous evaluation of an ACT-based intervention following stroke reached a moderate group-by-time effect (η2 = 0.07) on the Warwick and Edinburgh Mental Wellbeing Scale (51). Accordingly, a minimum sample of 52 participants is required to achieve statistical power for a linear mixed-effect model with a 2 (group) x 3 (time) design (80% power, α = 0.05). Allowing for an attrition rate of 10%, an N of 58 is adequate to perform the primary analyses.

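### The 10% minimum for fidelity rating does not ensure that each of the eight manual sessions, or both delivery modes, is independently rated

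*Protocol article*

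**What the plan says.** All sessions are video recorded. For fidelity, Table 1 (TIDieR checklist), item 11, specifies "a random selection of at least 10% of the video-recorded intervention sessions will be assessed by an independent researcher". Adherence is judged "using a checklist based on the manual for each session"; facilitation competence is scored on a 16-skill checklist with one added ACT item, the same for all sessions.

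The Intervention section describes the programme: "The program consists of eight 2-h group sessions delivered either in-person or" by telehealth, "with group sizes ranging from three to eight participants". Table 2 gives each session its own topic. Table 1, item 10, says that telehealth delivery shortened some activities, made some strategies optional and altered one exercise. Under Protocol Amendments Due to COVID-19, telehealth is analysed as a substitute for in-person delivery, not as a separate arm.

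The Abstract lists "treatment fidelity (manual adherence and therapist competence") among the criteria for trial feasibility, and the second aim in the Introduction includes "exploring the fidelity of delivering the intervention".

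The article gives neither the total number of groups nor the split by mode. It does not say whether the draw is stratified.

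**The concern.** The rule fixes a share of all recordings and says nothing about which sessions they come from. Because the adherence checklist is specific to the session, a rating of the sleep and fatigue session is no evidence that the content peculiar to the family and friends session was delivered. A session number that is not drawn has no independent adherence rating at all. In a trial of this size 10% is a handful of recordings, set against eight session types and two modes of delivery.

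At stake is how complete the fidelity evidence for a Phase III trial would be: which parts of the manual were delivered as written, and whether the telehealth version was delivered as faithfully as the in-person version with which it is pooled.

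**Working it through.** The plan gives no derivation for the 10%, so there is no figure of its own to reproduce on this point. The sample size used below is consistent: 52 / (1 − 0.10) = 57.8, rounded up to the stated 58.

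**Inputs from the article**
- Sample: 58 after allowing for attrition; "maximum possible sample size during the data collection period (*N* = 64") (Sample Size Calculation).
- Allocation 2:1 (Randomization and Blinding), so the intervention arm is 58 × 2/3 = 38.7, about 39, up to 64 × 2/3 = 42.7, about 43.
- Eight sessions per group, 3 to 8 participants per group (Intervention).

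**Assumption: number of groups, G.** Counting only participants randomised to the intervention, 39/8 = 4.9 and 43/3 = 14.3, so G is about 5 to 14. At the middle group size of 5.5, 43/5.5 = 7.8, about 8 groups.

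**Recordings at the minimum.** There are 8G sessions, of which k = 0.10 × 8G, rounded up, are rated. At least 8 − k session numbers are unrated whenever k is below 8, whatever the sampling scheme.

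**Coverage under an unstratified draw of exactly k**, by inclusion–exclusion:

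P(all eight rated) = Σ (−1)^j C(8, j) C((8 − j)G, k) / C(8G, k), for j = 0 to 8.

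For G = 9, k = 8, this reduces to 9^8 / C(72, 8) = 43,046,721 / 11,969,016,345 = 0.0036. For G = 10, k = 8, it is 10^8 / C(80, 8) = 100,000,000 / 28,987,537,150 = 0.0034.

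| Groups | Sessions | Rated at minimum | Unrated with certainty | P(all eight rated) | P(2 or more unrated) | P(3 or more unrated) |
|---|---|---|---|---|---|---|
| 5 | 40 | 4 | at least 4 | 0 | 1 | 1 |
| 6 | 48 | 5 | at least 3 | 0 | 1 | 1 |
| 7 | 56 | 6 | at least 2 | 0 | 1 | 0.90 |
| 8 | 64 | 7 | at least 1 | 0 | 0.97 | 0.72 |
| 9 | 72 | 8 | – | 0.004 | 0.91 | 0.54 |
| 10 | 80 | 8 | – | 0.003 | 0.91 | 0.55 |
| 12 | 96 | 10 | – | 0.038 | 0.70 | 0.26 |
| 14 | 112 | 12 | – | 0.119 | 0.47 | 0.11 |

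**Delivery mode.** If g groups used a given mode throughout, P(that mode is never rated) = C(8(G − g), k) / C(8G, k). For G from 5 to 14 this is 0.37 to 0.41 when g = 1 and 0.12 to 0.15 when g = 2. For g = 3 it is at most 0.05.

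**If more than the minimum is rated.** With 8 groups, 20% (13 recordings) gives P(1 or more unrated) = 0.79 and P(2 or more) = 0.31; 30% (20 recordings) gives 0.30 and 0.02.

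**The case against.** Several counter-arguments have force.

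- **The draw may be stratified.** The article says only that selection is random, and the full protocol may add strata. This stands, so the unstratified probabilities are conditional on that reading. It does not rescue the minimum with up to 8 groups, where fewer than eight recordings cannot cover eight sessions under any scheme.
- **The 10% is a lower bound.** The team may rate more, and the risk then falls sharply. That also stands, but the text commits to no more than 10%.
- **Overall fidelity survives.** A random sample estimates average adherence without bias. Homework review, values work, committed actions and barriers recur across sessions, the competence checklist is common to all sessions, and the senior facilitator monitors every session. All of this stands, although that monitoring is not independent rating.
- **Little hangs on it.** The aim is to explore fidelity, and Feasibility and Acceptability Measures sets no fidelity threshold. Recordings are kept for 7 years, so gaps could be filled later.

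A reader might infer that several sessions will almost certainly be missed. That holds for about 5 to 7 groups, where three or more are missed with probability 0.90 or higher. It weakens to 0.54 to 0.72 at 8 to 10 groups and fails at 12 to 14 (0.26 to 0.11). A reader might also infer that a whole delivery mode is likely to be missed. That is a material risk only if one mode was used by one or two groups, and the split is not given. The Discussion also mentions blended delivery, so mode need not be constant within a group.

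**Conclusion.** The concern holds in a limited form. As written, the rule does not guarantee an independent adherence rating for every manual session or for both modes. At the stated minimum, full coverage is impossible with up to 8 groups. With 9 to 14 groups it has a probability of about 0.3% to 12% if the draw is unstratified. These figures rest on an assumed 5 to 14 groups and on rating no more than the minimum.

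The documents do not support the stronger conclusion that the trial could not judge fidelity: average adherence and therapist competence remain estimable. The efficacy analysis is not touched. The loss is confined to adherence by session and, possibly, by mode, for a named feasibility outcome. This is a cheap improvement, not a flaw that threatens the trial.

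**What to change.** Replace the selection rule with one that draws at random at least one recording within each session number from 1 to 8. That makes a minimum of 8 recordings, or 10% of all sessions if that is larger. Spread the selected recordings over groups so that both in-person and telehealth delivery are included, with mode recorded for each session.

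The cost is small, because all sessions are already recorded and the same rater can score them. Compared with the present minimum, the extra recordings are 8 − 4 = 4 with 5 groups, 3 with 6, 2 with 7 and 1 with 8. None are needed from 9 groups (72 sessions) upward, where 10% already gives 8 or more.

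This does not rate every session in both modes. That would need 16 recordings, which is 25% of 64 sessions or 20% of 80, and is not required to close the gap described here.
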